#### Severe ear disease

CSOM, active: perforation of the TM with otorrhoea duration of more than 2 weeks, or TM with retraction pocket unable to see deepest part, with granulation tissue, squamous debris or otorrhoea.

### Protocol to deal with ears with incomplete data set

It is expected some subjects or ears would not have a complete data set. Reasons would include poor quality collection techniques, uploading error and the subjects not following through with seeing the island otolaryngologist or completing the audiogram at Bohol Hearing Centre.

When the CRF indicates otorrhoea and no other data are available/discernable, these ears are classified as CSOM. When the case report form indicates no otorrhoea or ear pain and only the tympanogram is available, the ears are classified either as normal or OME based on type A or types B/C, respectively. In ears without tympanograms, ear disease classification is solely based on video otoscopy. When the CRF notes no ear pain, tympanogram is missing and video otoscopy is missing/undiscernible, these ears are deemed ‘missing data’ and will not be included as part of the final analysis.

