#### Case report form (CRF)

Each research subject has an original paper CRF, which contains patient identifiers and clinical information entered by the research personnel following a parental interview with ear-specific medical history (ie, ear infection, discharge, TM perforation and hearing loss). CRFs collected during the week are uploaded by the research nurse into a Research Electronic Data Capture (REDCap) database hosted at the University of Colorado Denver School of Medicine, Aurora, Colorado, USA.

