#### Mild Ear Disease

Acute OM: the presence of at least two of the following three otoscopic signs: (1) white, yellow, amber or blue TM (ie, abnormal colour), (2) opacification not due to scarring, (3) tympanometry peak compliance <0.2 mL or tympanometric width >200 daPa on tympanometry, or bubbles or air-fluid interfaces, and one of the following three signs/symptoms: (a) ear pain, (b) redness of the TM and (c) fullness or bulging of the TM or acute purulent otorrhoea not due to otitis externa.^16–18^OM with effusion (OME): the presence of at least two of the following three otoscopic signs: (1) white, yellow, amber or blue TM (ie, abnormal colour), (2) opacification not due to scarring, (3) tympanometry peak compliance <0.2 mL or tympanometric width >200 daPa from tympanogram, or bubbles or air-fluid interfaces, and the absence of the following four signs/symptoms: (a) ear pain, (b) redness of the TM, (c) fullness or bulging of the TM or (d) acute purulent otorrhoea not due to otitis externa.^16–18^Healed perforation: otherwise normal TM with a thinned-out area of TM.Myringosclerosis: a hardening of the ear drum as calcium deposits form on the ear drum and middle ear, peak compliance on tympanogram >5.0 mL.

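### An ear with nothing but CRF otorrhoea is scored as CSOM (severe) without meeting the CSOM definition, and the incomplete-data rules give some such ears two outcomes and another group none

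*Protocol article*

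**What the plan says.** All references are to the protocol article.

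- **Severe ear disease.** The first limb of CSOM is "perforation of the TM with otorrhoea duration of more than 2 weeks". The alternative limb asks for a retraction pocket whose bottom is out of view, together with at least one of three further signs, of which discharge is one.
- **Protocol to deal with ears with incomplete data set.** The first rule reads "When the CRF indicates otorrhoea and no other data are available/discernable, these ears are classified as CSOM". Between this and the last rule stands one for ears with only a tympanogram, which names both otorrhoea and ear pain as symptoms that must be absent. The last rule begins "When the CRF notes no ear pain, tympanogram is missing and video otoscopy is missing/undiscernible, these ears are deemed"; its effect is that such an ear drops out of the final analysis. It names ear pain only.
- **Mild Ear Disease.** One of the signs of acute otitis media is "acute purulent otorrhoea not due to otitis externa".
- **Video-otoscopy data and diagnosis outcome classifications.** Box 1 separates otorrhoea from otitis externa, so the article recognises that discharge can have a non-otitis-media cause. The same section gives the subject the class of the worse ear.
- **Case report form (CRF).** The form holds clinical information entered by research personnel after a parental interview. Discharge is one of the history items, and no duration or time window is stated for it.

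**The concern.** The most serious label goes to the ears with the least evidence. A CRF entry of otorrhoea, with nothing else, shows no perforation, no retraction pocket, no duration and no cause. Under the article's own definitions the same entry could belong to a mild category or to a non-otitis-media diagnosis.

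The rules also fail to sort these ears uniquely. Two analysts following the text could place the same ear in the severe category or outside the analysis.

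The situation is foreseeable. Active otorrhoea leads to referral to the local otolaryngologist, and the incomplete-data section expects that some subjects will not attend. One such ear makes the whole subject severe through the worse-ear rule, and the ear disease classification is what the Statistical analysis methodology section compares between vaccine and placebo.

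**Working it through.** **1. The otorrhoea rule against the CSOM definition.** Limb one needs a perforation and a duration of more than 2 weeks. Limb two needs a retraction pocket whose deepest part is not visible, plus one further sign. Otorrhoea alone meets neither limb.

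**2. Sorting the ears.** Take an ear with no tympanogram and no usable video, and apply every rule in the incomplete-data section:

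| Otorrhoea on CRF | Ear pain on CRF | Rules that apply |
|---|---|---|
| yes | yes | CSOM |
| yes | no | CSOM and excluded as missing |
| no | no | excluded as missing |
| no | yes | none |

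One cell has two outcomes, one has none, and no precedence is stated.

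**3. Effect of false CSOM on VE.** The article gives no CSOM rate, effect size or missing-data rate, so there is no figure to reproduce and every input here is an assumption: true CSOM 1% in placebo, true VE 50% (hence 0.5% in the vaccine arm), and a false-CSOM rate f that is equal in both arms.

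Observed VE = 1 − (0.005 + f)/(0.01 + f)

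- f = 0.2%: 1 − 0.007/0.012 = 1 − 0.583, about 42%
- f = 0.5%: 1 − 0.010/0.015 = 1 − 0.667, about 33%
- f = 1%: 1 − 0.015/0.020 = 1 − 0.75 = 25%

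To place the value 0.2%: 12 000 subjects have 24 000 ears. If 5% lack examination data, that is 1200 ears. If 2% of those have CRF otorrhoea, that is 24 ears. If all 24 are false and in different subjects, 24/12 000 = 0.2%. The cohort size is the article's potential figure before attrition; the two percentages are assumed.

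**4. Effect of selective inclusion.** Suppose the CSOM sentence prevails. Let p be the true severe prevalence and m the share of ears without examination data. Assume that severe ears in that share are kept through their otorrhoea and the others are dropped.

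Observed prevalence = p / [p + (1 − p)(1 − m)]

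With p = 2%:

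- m = 5%: 0.02/0.951 = 2.1%
- m = 10%: 0.02/0.902 = 2.2%
- m = 20%: 0.02/0.804 = 2.5%

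For the comparison of arms, this selection multiplies the odds ratio by (1 − m in one arm)/(1 − m in the other). With equal m the factor is 1.00. With 10% against 15% it is 0.90/0.85 = 1.06, and with 5% against 15% it is 0.95/0.85 = 1.12.

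**The case against.** The strongest defence is that these are fallback rules, needed because the full definitions cannot be checked. The tympanogram-only rule works the same way: a type B or C trace alone becomes otitis media with effusion, although the full definition asks for two of three signs. A fallback that is looser than the definition is not an error in itself. That stands as a principle. It does not explain why a sign that the article also links to mild disease and to otitis externa should default to the severe category, and the article gives no reason.

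Second, the overlap is a single cell, and a reader taking the rules in order might let the otorrhoea rule win. A very strict reading of the condition that no other data exist, one that rules out even the CRF ear-pain item, would also remove the overlap. Both readings are possible, but the article states neither, and both leave the conflict with the CSOM definition in place.

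Third, an otolaryngologist's diagnosis entered in REDCap (Miscellaneous data) takes an ear out of the rule. This stands: the rule mainly affects subjects who do not attend the referral, and their number is unknown.

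Two stronger statements are tempting but unsupported. One is that the CRF entry is purely a parent's report and never an examination finding. The form is not shown, and it may record nurse observations or duration. The other is that CSOM is the rarest endpoint. The article calls it the most consequential complication and gives no rate for it.

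**Conclusion.** The point holds on the text. The otorrhoea rule assigns the severe category to ears that cannot be shown to meet its definition. For ears with neither tympanogram nor usable video, the rules are neither mutually exclusive nor complete. These rules are stated in the article and give conflicting endpoint values, so this is not detail left to an analysis plan.

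The consequence should not be overstated. A reader might infer that keeping ears with discharge and dropping symptom-free ones creates a spurious vaccine effect. The documents do not support that. Equal false-CSOM rates dilute VE towards the null, and equal missingness cancels from the odds ratio. A shift under the null needs missingness that differs by arm, which nothing in the article suggests.

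The size is unknown. The observed VE of about 42%, 33% or 25% rests on assumed placebo CSOM of 1%, true VE of 50%, and false CSOM in 0.2%, 0.5% or 1% of subjects in each arm. The 0.2% case corresponds to 24 affected ears, all false. The larger losses need 60 or 120 false-positive subjects among 12 000 (0.5% or 1%), and any true CSOM among the affected ears would reduce the dilution.

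**What to change.** Before analysis, reconcile the Severe ear disease definition with the incomplete-data section, so that each ear without a tympanogram and usable video falls under exactly one rule, including the ear with pain but no otorrhoea.

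- **Primary analysis:** count such an ear as CSOM only when other recorded data, for example the island otolaryngologist's diagnosis already in REDCap, meet the article's CSOM definition. Otherwise treat it as missing.
- **Sensitivity analysis:** repeat the comparison with CRF otorrhoea alone counted as CSOM.
- **Reporting:** give the number of affected ears by arm.

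The cost is a reworded paragraph and one extra table, with no new data collection. The downside is a few fewer CSOM events, some of which may be true; the sensitivity analysis shows how much that matters. Multiple imputation of these ears is an option and is not needed to resolve the point.

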#### Video-otoscopy and audiologic testing

Subjects whose TMs are devoid of cerumen or whose cerumen can be cleaned by the research nurses undergo video-otoscopy and audiologic testing. All subjects whose cerumen cannot be cleaned adequately are given a bottle of mineral oil and a medicine dropper and advised to use 5 drops twice a day for 7 days and asked to return for another assessment. However, subjects that fail to have adequate cerumen removal after the subsequent visit or had active otorrhoea are referred to the local otolaryngologist for further management

The research nurses record the two ears of a research subject in a regimented sequence for ease of review by the APPs at a subsequent time (right ear still photo, left ear still photo, right ear video and left ear video). SD cards are downloaded at the end of each weekday and images stored on two hard disks (original and backup disks). Data are transferred to the USA by external drives.

Audiologic testing data are processed in the following manner. The four discreet outputs produced by the tympanometer are used to determine tympanogram types. An overlay ‘rectangle’ onto the tympanometer tracing is used by the manufacturer to include most ‘normal’ tympanograms within these confines as defined by Jerger^13^ to assist with diagnosis. The local research team uses this real-time judgement call for a ‘pass’ or ‘fail’ depending if the peak of the tracing is within the ‘normal’ ranges as dictated by the ‘rectangle’. DPOAE results are also automatically determined by the device as either ‘pass’ or ‘refer’. Hearing screening done on subjects using the HearScreen device also classifies subjects as ‘pass’ or ‘fail’ by the device. All subjects who fail the tympanogram, DPOAE or HearScreen are referred to Bohol Hearing Centre for diagnostic audiometry. All raw tympanogram, automated DPOAE, automated HearScreen and raw HearX data are entered by the research supervisor to the REDCap database on a weekly basis.

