### Video-otoscopy data and diagnosis outcome classifications

Video-otoscopy analysis leading to disease classification takes into account all otoscopic abnormalities associated with acute OM, chronic non-suppurative OM and CSOM, as well as a non-OM diagnoses (eg, otitis externa) summarised in box 1. APPs document findings rather than immediately arrive at a diagnosis. Each video-otoscopic image is associated with a tympanogram type as to simulate pneumatic otoscopy, a proxy for the gold standard to diagnose middle-ear effusion.^14 15^ The gold standard for the presence of middle-ear fluid is detected only by myringotomy; however, this being impossible, the proxy methodology used here is based on the decisions made by the senior paediatric otolaryngologist with over 30 years of performing otologic procedures for complications from OM, including tympanoplasties and mastoidectomies. Given it would be impractical and impossible for the paediatric otolaryngologist to view thousands of video otoscopies, experienced otoscopists (APPs) have been trained and validated in identifying otoscopic abnormalities listed in box 1.

Box 1List of video-otoscopic finds depicting physical findings associated with otitis mediaRedness of tympanic membrane (TM).Opacification not due to scarring (dullness, thickened and webbing).Bubbles or air-fluid interfaces or fluid.Abnormal TM colour: white, yellow, amber or blue.Fullness or bulging of TM.Thinned out area of TM or healed perforation seen in 360°.Tympanosclerosis/scarring.Perforation small (<25% of TM).Perforation large (≥25% of TM).Retraction/retraction pocket/generally thinned out but not healed TM.Retraction/pocket bottom not seen.Otorrhoea not due to otitis externa (moisture).Granulation tissue or squamous debris.Otitis externa.

All video otoscopies that are deemed as poor quality by the APP are reviewed by the otolaryngologist of the study and would remained classified as poor quality or into one or more of the following TM findings.

Video-otoscopic findings for each ear will then merged with the four tympanometric output parameters and clinical medical history to arrive at discreet diagnoses (figure 1). Four broad diagnostic categories with definitions include normal, mild, moderate and severe ear disease. If two ears of a subject have disparate levels of middle-ear disease, the subject would be classified as having the more serious form of ear disease for the purpose of analysis.

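### Classifying ears without a tympanogram on video alone puts the perforation route to CSOM out of reach, so a confirmatory video can lower the severity class

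*Protocol article*

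**What the plan says.** All references are to the protocol article.

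- **General rule** (Video-otoscopy data and diagnosis outcome classifications): video findings for each ear are "merged with the four tympanometric output parameters and clinical medical history to arrive at discreet diagnoses".
- **Severe ear disease** consists of active CSOM, which has two limbs. The first is "perforation of the TM with otorrhoea duration of more than 2 weeks". The second is "or TM with retraction pocket unable to see deepest part, with granulation tissue, squamous debris or otorrhoea".
- **What the video supplies** (box 1): the relevant item is "Otorrhoea not due to otitis externa (moisture"), with no duration.
- **Where discharge history is held** (Case report form): the CRF, completed after a parental interview, covers "ear-specific medical history (ie, ear infection, discharge, TM perforation and hearing loss").
- **Incomplete data** (Protocol to deal with ears with incomplete data set): there are four rules. An ear with CRF otorrhoea and no other usable data is CSOM. An ear with only a tympanogram, and no otorrhoea or pain on the CRF, is normal or OM with effusion (OME) according to type. For the third case: "In ears without tympanograms, ear disease classification is solely based on video otoscopy". The fourth rule sets an ear to missing when the CRF notes no pain and both tests are absent or unreadable.

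**The concern.** Losing a tympanogram does not make the clinical history unusable, yet the third incomplete-data rule, as written, drops both. History is the only source the article describes that could supply how long an ear has been discharging, and the perforation limb of CSOM depends on that duration.

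The article calls CSOM the most consequential complication of otitis media and names it among the long-term outcomes on which the vaccine is to be evaluated. The worse ear sets the subject's class, so an ear-level error can pass to the subject. Vaccine and placebo are then compared on that classification. A severity class that depends on which test happened to be obtained, and that can fall when evidence is added, is a poor basis for the comparison.

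**Working it through.** No sample size, power or error-rate figure is involved, and the article gives no number to reproduce. The check takes one ear through the article's definitions, using only what box 1 allows a reader to record.

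**The ear.** Readable video, perforation with otorrhoea, otorrhoea noted on the CRF, no tympanogram.

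**Step 1: which incomplete-data rule applies.** The CRF-only otorrhoea rule requires that nothing else be available or discernible. A readable video excludes it, so the video-only rule applies.

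**Step 2: each class under video alone.**

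| Class | Requirement | Met on video alone? |
|---|---|---|
| Severe: CSOM, perforation limb | Perforation and otorrhoea for more than 2 weeks | No. Duration is not a box 1 item |
| Severe: CSOM, retraction-pocket limb | Pocket with unseen depth, plus granulation, debris or otorrhoea | Only if such a pocket is present; all elements are in box 1 |
| Moderate: dry perforation | Perforation without otorrhoea, or ear canal volume of at least 2 mL | No. Otorrhoea is present and no volume was measured |
| Moderate: adhesive OM | Intact membrane with retraction | No. The membrane is perforated |
| Mild: acute OM or OME | At least two of abnormal colour, opacification, and bubbles or fluid levels (tympanometric criteria unavailable), plus the acute-sign condition | Only if those further signs are seen |
| Mild: healed perforation | Otherwise normal membrane with a thinned area | No |
| Mild: myringosclerosis | Calcium deposits | Only if these are also seen |
| Normal | No disease-related video finding | No |

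Unless the retraction-pocket limb applies, the ear is Mild because of other signs or fits no defined class.

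**Step 3: remove the video.** With CRF otorrhoea and neither test usable, the first incomplete-data rule makes the same ear CSOM, with no duration requirement.

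**Step 4: compare.**

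- CRF otorrhoea, no video, no tympanogram: Severe.
- CRF otorrhoea, video confirming a draining perforation, no tympanogram: Mild or unclassified.

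The second ear has more evidence of disease and receives a lower class. The two rules are therefore inconsistent with each other, and the third is also inconsistent with the general rule that uses history.

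**Step 5: size.** A count would need the rate of missing tympanograms, the rate of draining perforations, the share of those with a readable video, and the share of subjects whose other ear is already Severe. The article gives none of these, so no count is computed.

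**The case against.** **The rule may mean only that tympanometry is left out.** On that reading, video replaces the video-plus-tympanogram pair and history is still merged as usual. This is possible, and the classification figure is not available to settle it. The wording does not favour it: the other three incomplete-data rules each name the CRF when they use it, while this one omits it and makes video the sole basis. If the milder meaning is intended, the sentence still needs correcting, because it can be programmed literally.

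**Discharging ears get a specialist opinion.** Subjects who "had active otorrhoea are referred to the local otolaryngologist for further management", and the island otolaryngologist's diagnoses are entered in REDCap. This stands as a possible source of information. However, the article does not say that such a diagnosis enters the classification or overrides the video-only rule.

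**The affected group may be small.** It is limited to ears with a readable video, no tympanogram, a perforation, otorrhoea and no qualifying retraction pocket. That is correct and limits what can be claimed.

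**History may not hold the duration.** The article lists discharge among the CRF items but not how long it lasted. This also stands. Restoring the CRF alone may not bring back the perforation limb, so the fix must cover an unrecorded duration.

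**Conclusion.** The point holds as a contradiction between stated rules. Read as written, the video-only rule makes the perforation limb of CSOM unreachable for ears without a tympanogram and gives a draining perforation a lower class than the CRF-only rule gives with less evidence. This rests on the literal reading of the rule and on box 1 being the full list of what video readers record.

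Three stronger conclusions might be inferred, and the documents do not support them:

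- *Ears without a tympanogram can never be Severe.* The retraction-pocket limb can be read from video alone.
- *Severe disease is under-counted overall, by some estimable number.* Ears with CRF otorrhoea and neither test usable go to CSOM without any duration, which could over-count. The net direction is unknown. Any figure would rest on assumed rates and would also have to allow for the readable-video condition and the worse-ear rule.
- *Tympanograms are missing mainly in wet or perforated ears.* The article does not say so. It uses ear canal volume as a criterion for dry perforation, so it expects usable tympanometry in at least some perforated ears. Referral of active otorrhoea does not establish that testing was skipped.

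Nor can a difference between vaccine and placebo be derived. The correction is worth making because it is cheap and concerns the most serious outcome class.

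**What to change.** Reconcile the general classification rule, the Severe definition and the incomplete-data section. Replace the video-only sentence with a rule to this effect:

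*An ear without a tympanogram is classified from video otoscopy together with the CRF ear history and any otolaryngologist diagnosis held in REDCap, using the Mild, Moderate and Severe definitions with tympanometric criteria treated as unavailable. A perforation with otorrhoea of unrecorded duration is assigned to one named class, consistent with the rule for ears with CRF otorrhoea and no other data.*

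As the CRF-only rule now stands, consistency means CSOM. If the study team prefers another class, both rules should change together. The choice should be fixed before ear disease is compared between arms.

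The cost is the amended rule and a change to the classification algorithm. CRFs and otolaryngologist diagnoses already go into REDCap, so combining them with the video needs no new data collection. The drawback is reliance on parent-reported discharge, which the CRF-only rule already accepts. The change affects outcome coding only, not the care of any subject.
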